### Study Instruments

The primary endpoint being evaluated is the rate of participation in colorectal cancer screening between the two intervention arms (Sequential Choice, Active Choice) versus the control arm (colonoscopy only). The FIT is a well validated tool for colorectal cancer screening and is one of the screening modalities recommended by the USPSTF. The control arm will be sent a letter inviting them to schedule screening colonoscopy directly through the Gastroenterology Call Center. If not scheduled within 4 weeks, subjects will receive a mailed reminder to call to schedule. The Sequential Choice arm will be sent the same initial outreach as the control arm. If not scheduled within 4 weeks, subjects will receive a mailed reminder including the call center number as well as the option to complete a FIT kit mailed along with the reminder. The Active Choice arm of the study will be sent a letter offering the choice of Colonoscopy or completion of the FIT kit included with the initial mailing. If subjects in this group have not either scheduled colonoscopy nor completed FIT within 4 weeks, they will receive a mailed reminder to call to schedule colonoscopy or to complete the original mailed FIT.

A sub-sample of 90 subjects will be called to complete a questionnaire over the phone ~~4~~**beginning approximately 6** months after initial outreach was mailed. ~~The subjects will be asked to confirm their eligibility (e.g. that they had not had CRC screening within the USPSTF CRC screening guidelines) and provide additional demographic and socioeconomic information so that we can better understand what populations, if any, may have differential response rates. We will also ask them~~ **The subjects will be asked to explain their experience with CRC screening prior to our initial outreach (November 2017), as well as about their perception of the impact and design of CRC screening outreach. Additional questions will probe for potential barriers to screening participation and ways to improve participation in the future.** ~~Demographic and socioeconomic questions are modified from demographic questions on the Behavioral Risk Factor Surveillance System survey, administered by the Centers for Disease Control and Prevention. See attached sub-sample questionnaire.~~

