#### 1.2. Data Analysis

The primary outcome is CRC screening completion (FIT or colonoscopy) within 4 months of initial outreach. We will conduct a chi-square analysis using Stata to compare arms 2 and 3 to arm 1 separately using intent-to-treat protocol. We will also compare arms 2 and 3 as a secondary analysis. We will quantitatively analyze the choice of screening test and evaluate the survey results by study arm. As exploratory analyses, we will evaluate response by practice location, age, gender, race/ethnicity, and income at the level of zip code.

Analysis will be conducted by blinded members of the research team at least four months after the last FIT is mailed.

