**2) Prior to November 2017, had you ever been screened for colon cancer before? Y/N**

If N: question 3

If Y: which test?

If Y: do you remember when?

If Y: do you remember where it was done?

**3) In November 2017, we mailed you an invitation to participate in colon cancer screening. What was your experience with that invitation?**

(if no recollection/didn't receive it, skip to question 5)

**4) Our records show that you didn't complete FIT/Colonoscopy after receiving that invitation. Don't worry – you're not alone, many people didn't! Can you tell me about how that invitation helped you think about getting yourself screened for colon cancer? What are some of the reasons you decided not to get it done? What would facilitate you getting screened in the future?**

or

Our records show that you completed FIT/Colonoscopy after receiving that invitation – that's fantastic! **Can you tell me about how that invitation helped you think about getting yourself screened for colon cancer? What are some of the reasons you decided to get it done?**

- a. Follow-up: **Good or bad, we'd love to hear your screening story so we can capitalize on our strengths and improve where we fall short. Can you tell us about this colon cancer screening experience?** (Convenience/ease, prep, time it took, confidence in process/results, repeat, what would you tell others about it?)

113 5) The FIT test is an at-home screening test for colon cancer where you send a swab of stool to the lab to  
114 test for blood. Most doctors want their patients who are 50-75 years old to either do this test once per  
115 year, or get a colonoscopy once every ten years. **In the future, would you prefer to have a colonoscopy**  
116 **every 10 years or take a FIT every year?**

- 117 a) FIT
- 118 b) Colonoscopy
- 119 c) No preference
- 120 d) Prefer not to be screened

121  
122 6) Can you tell us more about why FIT/Colonoscopy is your preference?

123  
124 7) What would be the most helpful thing Penn Medicine could do to help ensure you get screened for  
125 colon cancer regularly?

126  
127 Thank you for taking the time to give us your input, we appreciate it!

128 If you have any questions about this call, the FIT kit, colonoscopy or colon cancer screening in general, please  
129 call us at XXX-XXX-XXXX or speak with your Doctor.

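### Interview question 4 presupposes that the invitation helped, which tilts perceived-impact answers towards the positive among respondents who recall it

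*Supplement*

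**What the plan says.** The final protocol (Study Instruments) describes a telephone interview of a random sub-sample. It covers earlier screening experience, "as well as about their perception of the impact and design of CRC screening outreach", barriers, and ways to improve participation. Final SAP section 1.2 plans to "evaluate the survey results by study arm". Section 1.6 of the final protocol classes these data as exploratory and qualitative.

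The script is in Appendix A:

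- **Question 3** is open and neutral: "What was your experience with that invitation". It carries a routing instruction: "if no recollection/didn't receive it, skip to question 5".
- **Question 4** then branches on whether the records show a completed FIT or colonoscopy. Non-completers first hear "you're not alone, many people didn't"; completers first hear "that's fantastic". Both branches continue with the same stem: "Can you tell me about how that invitation helped you think about getting yourself screened for colon cancer".
- Both branches then ask for the reasons behind what the respondent *decided*. Non-completers are also asked what would make screening easier in future.

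**The concern.** The stem takes it as given that the invitation helped and asks only in what way. Its wording has no *if at all* and does not mention that the letter might have made no difference or put the person off. A respondent who felt no effect has to contradict the caller's premise, and the caller speaks for the respondent's own practice. For non-completers the mismatch is sharpest: they have just been told that they were not screened, and are then asked how the letter helped.

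Two further features add to this. The opening remark is evaluative and depends on the outcome, so any contrast between the reasons of completers and non-completers is also a contrast between praised and reassured respondents. The reasons item assumes a deliberate decision, which fits poorly with someone who forgot, or who booked and did not attend. Barriers of that kind are among the things the interview is meant to find.

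At stake is the usefulness of the perceived-impact material. Accounts of helpfulness are likely to lean positive, and the respondents best placed to say why a letter failed get the least suitable prompt.

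**Working it through.** The point is mainly one of wording. Arithmetic shows only who would hear which version.

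**1. The plan's own figure.** The final protocol (Administration of Surveys and/or Process) selects 90 subjects and expects to reach about 50%: 90 × 0.50 = 45, and 45 / 3 = 15 per arm. This reproduces the stated 45 and 15.

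**2. Who would hear which branch.** Final SAP section 1.1 gives 5% completion in control and an 11-point increase in each choice arm, so 5% + 11% = 16%. Assume that interviewees complete at these rates.

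| Arm | Interviewed | Completers | Non-completers |
|---|---|---|---|
| Colonoscopy only | 15 | 15 × 0.05 = 0.75 | 14.25 |
| Sequential choice | 15 | 15 × 0.16 = 2.40 | 12.60 |
| Active choice | 15 | 15 × 0.16 = 2.40 | 12.60 |
| Total | 45 | 5.55 | 39.45 |

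About 39 of 45 would be routed to the reassurance branch and 5 to 6 to the praise branch. These are upper limits, because anyone who does not recall the invitation skips question 4. The documents give no recall rate.

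**3. Difference between arms.** The stem is identical in every arm. Only the opening remark varies, through completion: 14.25 − 12.60 = 1.65 people per 15, or 95% against 84%.

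**4. Reading the items side by side.** Question 3 asks about experience of the invitation without a premise. Question 4 is the only item that asks directly what the invitation did to the respondent's thinking, and it carries the premise. The cue welcoming good or bad accounts is printed as a follow-up under the completer branch. It concerns the screening experience, not the invitation. Questions 5 to 7 ask about future preference and about help from the health system.

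**5. Size of the shift in answers.** The documents give nothing from which to estimate it, so none is assumed.

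**The case against.** The strongest reply is that this is one open question in a small exploratory interview with safeguards around it. The introduction tells respondents that no answer is wrong. Question 3 is neutral and comes first. Question 4 has no response scale, so a respondent can say that the letter did nothing and have that recorded. Non-completers are asked directly why they were not screened. Reassurance may make it easier to admit non-completion, so the remarks are partly a matter of interviewing style. Any question about why or why not must branch on outcome anyway.

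Most of this stands, and it rules out several stronger readings that a reader might infer:

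- *Everyone is asked the leading question.* The skip after question 3 removes those with no recollection or receipt of the invitation.
- *The interview cannot show that an outreach had no effect.* It can, at question 3 or by a respondent contradicting the premise at question 4. The wording makes that less likely. In any case, the trial tests the effect of outreach by the randomised comparison of screening completion.
- *The remarks bias the later preference and suggestions.* Carry-over is possible but not shown. Question 5 has its own introduction, offers no preference and no screening as answers, and also goes to people who skipped question 4.
- *The wording distorts the comparison by arm.* The stem is common to all arms, and the opening remark differs in exposure by only about 1.65 people per 15.

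The safeguards do not make the stem itself neutral.

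**Conclusion.** The point holds as a minor one. Among respondents who recall the invitation, question 4 presupposes benefit on a stated interview topic, so answers on helpfulness are likely to lean positive in all arms. The outcome-dependent remarks and the assumption of a deliberate decision weaken the reasons data further. The direction is a judgement from the wording; its size is unknown. The count of about 39 non-completers in 45 assumes that interviewees complete at the planning rates, and it is a ceiling because of the skip. The data are exploratory, and the randomised primary analysis is untouched.

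**What to change.** In both branches of question 4:

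- Replace the stem with: *How, if at all, did that invitation affect your thinking about getting screened for colon cancer?* This keeps the item on thinking about screening. Asking instead what caused the respondent to be screened or not would change what is measured, and would miss a letter that moved thinking without moving completion.
- Replace the reasons item with: *What were the main reasons you did / did not get screened?*
- Preferably use one neutral lead-in for both branches, with any courtesy remark after question 7.

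Flag interviews already done with the current wording, and report their helpfulness answers as elicited by a leading prompt.

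The cost is a wording amendment to the script, with no extra patients, calls or staff. The downsides are a slightly less warm script and, if interviews have started, two wordings in a sample of about 45.

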## Appendix B – Mailed Outreach Language

### Initial Outreach

#### **Colonoscopy Only**

Our records show that you may be overdue for your colon cancer screening  
Penn Medicine is offering a special VIP hotline to patients for scheduling screening colonoscopy.  
Please call XXX-XXX-XXXX to schedule your colonoscopy right away.

Call the VIP hotline XXX-XXX-XXXX to schedule your screening colonoscopy today!

#### **Sequential Choice**

Our records show that you may be overdue for your colon cancer screening  
Penn Medicine is offering a special VIP hotline to patients for scheduling screening colonoscopy.  
Please call XXX-XXX-XXXX to schedule your colonoscopy right away.

Call the VIP hotline XXX-XXX-XXXX to schedule your screening colonoscopy!

#### **Active Choice**

Our records show that you may be overdue for your colon cancer screening  
Penn Medicine is offering a special VIP hotline to patients for scheduling screening colonoscopy.  
Please call XXX-XXX-XXXX to schedule your colonoscopy right away.  
Alternatively, you may choose to instead complete and return the enclosed stool test called FIT (Fecal  
Immunochemical Test).

Call the VIP hotline XXX-XXX-XXXX to schedule your screening colonoscopy  
-or-  
complete and return your FIT today!

189  
190  
191  
192  
193  
194  
195  
196  
197  
198  
199  
200  
201  
202  
203  
204  
205  
206  
207  
208  
209  
210  
211  
212  
213  
214  
215  
216  
217  
218  
219  
220  
221  
222  
223  
224

**Reminder Outreach**

**Colonoscopy Only**

Our records show that you may be overdue for your colon cancer screening  
Penn Medicine is offering a special VIP hotline to patients for scheduling screening colonoscopy.  
Please call XXX-XXX-XXXX to schedule your colonoscopy right away.

Call the VIP hotline XXX-XXX-XXXX to schedule your screening colonoscopy today!

**Sequential Choice**

Our records show that you may be overdue for your colon cancer screening  
Penn Medicine is offering a special VIP hotline to patients for scheduling screening colonoscopy.  
Please call XXX-XXX-XXXX to schedule your colonoscopy right away.  
Alternatively, you may choose to instead complete and return the enclosed stool test called FIT (Fecal  
Immunochemical Test).

Call the VIP hotline XXX-XXX-XXXX to schedule your screening colonoscopy  
-or-  
complete and return your FIT today!

**Active Choice**

Our records show that you may be overdue for your colon cancer screening  
Penn Medicine is offering a special VIP hotline to patients for scheduling screening colonoscopy.  
Please call XXX-XXX-XXXX to schedule your colonoscopy right away.  
Alternatively, you may choose to instead complete and return the enclosed stool test called FIT (Fecal  
Immunochemical Test).

Call the VIP hotline XXX-XXX-XXXX to schedule your screening colonoscopy  
-or-  
complete and return your FIT today!
